## Abstract

**Background:**

Ischemic stroke remains a leading cause of disability worldwide. Early rehabilitation is crucial for functional recovery. Electric tilt table (ETT) training improves motor and balance function and facilitates early mobilization in bedridden patients, but its use is often limited by orthostatic hypotension (OH). Enhanced external counterpulsation (EECP), a noninvasive circulatory support technique, has shown benefits in cardiovascular and cerebrovascular diseases by improving vascular function and cardiac output. Given its hemodynamic effects, EECP may enhance tolerance to verticalization. However, whether early sequential application of EECP followed by ETT training improves functional recovery after ischemic stroke remains unclear. This study aims to determine whether this sequential strategy improves neurological and functional recovery while reducing symptomatic orthostatic hypotension in patients with ischemic stroke.

**Methods:**

This single-center, randomized controlled clinical trial will be conducted at Beijing Rehabilitation Hospital, Capital Medical University. A total of 104 participants with ischemic stroke within 3 months of onset will be enrolled and randomly allocated in a 1:1 ratio to either the ETT training group (conventional rehabilitation plus once-daily 30-min ETT training) or the sequential EECP - ETT training group (conventional rehabilitation plus once-daily 60-min EECP immediately followed by 30-min ETT training). Both interventions will be delivered 5 days per week for 7 weeks. The primary outcome is overall neurological function at week 7, assessed by the National Institutes of Health Stroke Scale (NIHSS). Secondary outcomes include the incidence of symptomatic OH during ETT training sessions, motor function (Fugl-Meyer Assessment, FMA), balance (Berg Balance Scale, BBS), swallowing (Modified Mann Assessment of Swallowing Ability, MMASA), activities of daily living (Barthel Index, BI), and noninvasive hemodynamic parameters (cardiac index, stroke volume, systemic vascular resistance index) assessed at week 7. Outcome assessments will be performed by blinded evaluators. Safety will be monitored throughout the study period.

**Discussion:**

This study will evaluate the sequential application of EECP and ETT in early ischemic stroke rehabilitation. The findings will clarify whether this strategy safely alleviates symptomatic orthostatic hypotension and promotes overall functional recovery, potentially offering an effective and integrative approach for early stroke intervention.

**Trial registration:**

http://www.chictr.org.cn, Chinese Clinical Trial Registry, ChiCTR2400083761. Registered on April 30, 2024.

## Background

Ischemic stroke remains a major public health challenge worldwide, characterized by high incidence, substantial disability, and considerable mortality (1, 2). While early systematic rehabilitation is essential for functional recovery, traditional motor therapies offer limited efficacy (3, 4). For bedridden patients, early verticalization is imperative to restore consciousness, activate musculature, and improve motor stability (5–7). Although the electric tilt table (ETT) training is a standard tool for verticalization, its utility is often constrained by orthostatic hypotension (OH) (8–11). OH is common during inpatient stroke rehabilitation, affecting nearly half of patients; symptomatic OH occurs in approximately one-third of patients (12). Because ETT training involves progressive verticalization, OH may be precipitated or exacerbated during training. Symptomatic OH is of particular concern because it may interrupt rehabilitation sessions, limit tolerance to early mobilization, and compromise rehabilitation progress (13). Given the lack of definitive treatments for OH, targeted pre-conditioning strategies are required to enhance orthostatic tolerance (14).

Enhanced external counterpulsation (EECP) is a noninvasive circulatory support technique that augments venous return and cardiac output, improving perfusion to the heart and brain (15–18). Beyond its established therapeutic benefits, EECP’s hemodynamic effects suggest potential as a pre-conditioning strategy. By stabilizing vascular tone and increasing systemic perfusion prior to verticalization, EECP may mitigate OH and improve tolerance to ETT training (19). However, evidence regarding the sequential integration of these modalities remains scarce.

Consequently, we hypothesize that the early sequential application of EECP followed by ETT training synergistically promotes neurological and functional recovery in patients with ischemic stroke. This study aims to evaluate the clinical feasibility, efficacy, and safety of this integrative approach. We will assess its impact on neurological, motor, balance, and swallowing functions, alongside activities of daily living and noninvasive hemodynamic parameters (Figure 1). If validated, this strategy could optimize rehabilitation efficiency, providing evidence for a safe and accelerated early recovery pathway in stroke patients.

**Figure 1 fig1:**
[figure not shown]
Conceptual framework of the study design. BBS, Berg Balance Scale; BI, Barthel Index; CI, Cardiac Index; EECP, Enhanced External Counterpulsation; ETT, Electric tilt table; FMA, Fugl-Meyer Assessment; MMASA, Modified Mann Assessment of Swallowing Ability; NIHSS, National Institutes of Health Stroke Scale; SV, Stroke Volume; SVRI, Systemic Vascular Resistance Index.

## Methods

### Study design

This single-center, randomized controlled clinical trial will be conducted at Beijing Rehabilitation Hospital, Capital Medical University, and has been registered with the Chinese Clinical Trial Registry (ChiCTR2400083761). The protocol adheres to the Standard Protocol Items: Recommendations for Interventional Trials guidelines (20), the Declaration of Helsinki (21). It has been approved by the institutional Ethics Committee and will be overseen by the Department of Scientific Research Management of the Beijing Rehabilitation Hospital, Capital Medical University. Following the acquisition of written informed consent, enrolled participants will undergo a 7-week study period. The detailed trial workflow is depicted in Figure 2.

**Figure 2 fig2:**
[figure not shown]
Study flowchart of trial process. BBS, Berg Balance Scale; BI, Barthel Index; CI, Cardiac Index; EECP, Enhanced External Counterpulsation; FMA, Fugl-Meyer Assessment; MMASA, Modified Mann Assessment of Swallowing Ability; NIHSS, National Institutes of Health Stroke Scale; SV, Stroke Volume; SVRI, Systemic Vascular Resistance Index.

### Participants

Patients diagnosed with ischemic stroke undergoing rehabilitation at Beijing Rehabilitation Hospital, Capital Medical University, will be screened for eligibility.

Eligible participants must meet all of the following inclusion criteria: (1) aged ≥ 18 years; (2) first-ever stroke, or recurrent stroke without residual limb motor or consciousness deficits attributable to the previous stroke, with onset time <3 months; and (3) provision of written informed consent by the patient or a legally authorized representative.

Candidates will be excluded from the study if they meet any of the following criteria: (1) hemorrhagic disorders or the use of oral anticoagulants posing a bleeding risk; (2) rheumatic heart disease; (3) moderate-to-severe aortic regurgitation and/or stenosis; (4) aortic dissection, thoracoabdominal/cerebral aneurysm, or vascular malformation; (5) moderate-to-severe pulmonary hypertension, right ventricular dysfunction, or decompensated left heart failure; (6) uncontrolled severe hypertension (blood pressure >170/110 mmHg); (7) uncontrolled arrhythmias, (e.g., frequent premature contractions, ectopic tachycardia, second- or third-degree atrioventricular block, or other clinically significant rhythm disturbances); (8) active thrombophlebitis or deep vein thrombosis; (9) local skin infection or moderate-to-severe edema at the cuff placement sites; (10) severe symptomatic peripheral vascular disease or prior lower-limb arterial stenting implantation; (11) active malignancy; or (12) pregnancy.

Eligibility will be determined by the investigators based on participants’ medical history, review of medical records, routine laboratory tests, and pre-enrolment clinical assessments. All participants will undergo electrocardiography, 24-h Holter monitoring, transthoracic echocardiography, and lower-extremity vascular ultrasonography before enrolment. Additional examinations will be performed when clinically indicated to confirm eligibility or exclude potential contraindications.

Participants will be withdrawn from the trial under any of the following conditions: (1) withdrawal of informed consent; (2) requirement for prohibited concomitant therapies or procedures that may confound study outcomes; or (3) loss to follow-up or relocation precluding scheduled assessments.

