### Interventions

All participants will receive standard of care, consisting of conventional rehabilitation therapy and comprehensive nursing care. Specific interventions related to the study groups will be administered in addition to this baseline therapy.

Monitoring and Nursing Care: Participants will undergo continuous clinical observation and hemodynamic monitoring. Standardized nursing protocols will be implemented, including the management of indwelling catheters, anti-spasticity limb positioning, nutritional support, medication reconciliation, and psychological counseling.

Rehabilitation therapy: Personalized rehabilitation programs will be formulated by a multidisciplinary team, incorporating data from physical examinations, laboratory results, and functional assessments. Depending on clinical indications, therapeutic modalities may include acupuncture, Chinese therapeutic massage (Tuina), swallowing therapy, cognitive rehabilitation, and speech-language interventions. Neurological status and functional progress will be systematically reassessed to titrate treatment intensity and adjust rehabilitation plans accordingly.

Communication and education: To ensure treatment adherence, clinicians will provide structured health education to patients and their caregivers, covering disease progression and safety precautions. Formal informed consent will be obtained prior to the initiation of each specific therapeutic modality.

ETT training group

Prior to the intervention, participants will be briefed on the principles and safety precautions of the ETT training to alleviate anxiety and optimize compliance. Patients will be positioned supine on the tilt table, with the thorax, pelvis, and knees secured by safety straps. A support board will be utilized for upper limbs stabilization, while the lower limbs remain extended with the feet resting firmly against the footboard. Participants will be instructed to maintain a relaxed, neutral posture throughout the procedure.

The training will initiate at a tilt angle of 30°. Following an initial 15-min tolerance period, the angle will be increased in increments of 10–15°, as tolerated by the patient. Each session will last 30 min, performed once daily, 5 days per week. Both the tilt angle and duration will be progressively adjusted based on the patient’s functional recovery. The primary therapeutic goal is to achieve tolerance of a 90° vertical position for 30 min without adverse symptoms or discomfort.

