Safety considerations: Potential transient adverse effects associated with EECP and ETT training include lower-limb discomfort, skin erythema or abrasion at the cuff contact sites, transient headache, dizziness, nausea, excessive sweating, orthostatic intolerance, and syncope. All adverse events will be documented throughout the study and managed according to predefined safety procedures. Participants who develop serious or intolerable intervention-related adverse events (e.g., refractory orthostatic hypotension, persistent arrhythmias, decompensated heart failure, or syncope requiring medical evaluation) or new contraindications to EECP or ETT (e.g., incident venous thrombosis or progression of aortic regurgitation), as determined by the investigators, will discontinue the study intervention. Unless they withdraw informed consent, these participants will continue scheduled follow-up assessments according to the study protocol. Training (either EECP or ETT) will be immediately discontinued if any of the following clinical conditions occur: marked fatigue, acute pain, agitation, profuse sweating, palpitations, chest tightness or angina, dyspnea, heart rate ≥120 bpm or ≤40 bpm, systolic blood pressure >180 mmHg or <90 mmHg, respiratory rate ≥35 breaths/min, oxygen saturation <90%, new-onset arrhythmias, or dynamic ST–T segment changes. Standardized medical management will be promptly initiated.

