### Statistical analysis

Continuous variables will be summarized as mean ± standard deviation if normally distributed or as median (interquartile range) otherwise. Categorical variables will be presented as frequencies and percentages. Group comparisons will be performed using the *t*-test for normally distributed continuous variables, the Wilcoxon rank-sum test for non-normally distributed data, and the chi-square or Fisher’s exact test for categorical variables. To account for potential baseline imbalances, group differences in primary and secondary outcomes at week 7 will be evaluated using Analysis of Covariance (ANCOVA), with the respective baseline scores included as covariates.

Analyses will be performed on both the intention-to-treat (ITT) and per-protocol (PP) populations, with the ITT set serving as the primary analysis population. Missing data in the ITT population will be handled using multiple imputation. Safety will be assessed in all participants receiving at least one intervention session. Adverse events and complications will be analyzed using chi-square or Fisher’s exact tests.

Exploratory subgroup analyses according to baseline stroke severity (baseline NIHSS score) will be performed to explore potential heterogeneity of treatment effects. Because the study is not powered for subgroup analyses, these analyses will be considered exploratory and interpreted cautiously.

All statistical analyses will be conducted using R software (version 4.2.2; R Foundation for Statistical Computing, Vienna, Austria). All tests will be two-sided with a significance level of 0.05. Statisticians will remain blinded to group allocation throughout the process.

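### Withdrawing patients from the trial because they need a prohibited or confounding therapy appears to cost their week-7 NIHSS, which weakens the ITT primary analysis

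*Protocol article*

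**What the plan says.** All references are to the protocol article.

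- **Participants.** The withdrawal rule opens with "Participants will be withdrawn from the trial under any of the following conditions". Condition (2) is "requirement for prohibited concomitant therapies or procedures that may confound study outcomes". It stands between withdrawal of informed consent, condition (1), and "loss to follow-up or relocation precluding scheduled assessments", condition (3).
- **Interventions, safety considerations.** Patients with serious or intolerable intervention-related adverse events, or with new contraindications, are treated differently: "as determined by the investigators, will discontinue the study intervention". The next sentence adds: "Unless they withdraw informed consent, these participants will continue scheduled follow-up assessments according to the study protocol".
- **Statistical analysis.** Both ITT and per-protocol analyses are planned, "with the ITT set serving as the primary analysis population". On incomplete data: "Missing data in the ITT population will be handled using multiple imputation".
- **Outcomes and Tables 1 and 2.** The primary outcome is NIHSS at week 7. NIHSS is scheduled at baseline and at week 7, with nothing in between.

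**The concern.** The article separates stopping the study intervention from leaving the trial, and it puts condition (2) on the leaving side. The need for another therapy arises after randomisation. It is plausibly linked to how the patient is recovering, and its frequency could differ by arm, because the trial's hypothesis is that EECP changes orthostatic tolerance and recovery. Participants and therapists know the allocation (Randomization and blinding), and whether a therapy may confound outcomes is a matter of judgement.

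An ITT comparison needs the week-7 NIHSS under the care the patient actually received. If a stated rule ends assessment for these patients, that value is never collected, and no later analysis can recover it. At stake are some loss of information and a possible bias in the primary comparison.

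**Working it through.** **1. The two rules side by side.**

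| | Participants, condition (2) | Interventions, safety |
|---|---|---|
| Trigger | need for a prohibited or confounding therapy | serious or intolerable adverse event, or new contraindication |
| What ends | participation in the trial | the study intervention |
| Assessments afterwards | not stated; listed with consent withdrawal and loss to follow-up | continue, unless consent is withdrawn |

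The retention sentence refers to the patients just described in the safety paragraph and does not reach the condition (2) group. One patient could also fall under both rules. Incident venous thrombosis is given as an example of a new contraindication, which means stop the intervention and stay in follow-up. Oral anticoagulants posing a bleeding risk are an exclusion criterion. If such treatment also counts as prohibited during the trial, which the article does not state, the two rules send the same patient in different directions.

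**2. The plan's own figures** (Sample size estimation: δ = 2.71, σ = 3.82, two-sided α = 0.05, power 90%, 20% dropout).

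- n = 2 × (1.960 + 1.282)² × 3.82² / 2.71² = 41.76, so 42 per group. This reproduces.
- 42 / 0.8 = 52.5 per group, or 84 / 0.8 = 105 in total. The stated 52 and 104 agree to within rounding.

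This point changes none of these figures.

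**3. Information lost.** Power on observed outcomes with m per arm is Φ(δ / (σ√(2/m)) − 1.96). The extra loss is assumed, because the article gives no rate for condition (2) exits.

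| Loss beyond the budgeted 20% | m = 52 × (1 − loss) | Power |
|---|---|---|
| 0 points | 41.6 | 89.9% |
| 5 points | 39.0 | 88.0% |
| 10 points | 36.4 | 85.7% |
| 15 points | 33.8 | 83.1% |

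If these exits are already inside the 20% allowance, the first row applies.

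**4. Bias.** Let w_C and w_E be the shares withdrawn under condition (2) in the ETT and EECP-ETT arms. Let d be the number of NIHSS points by which withdrawn patients would truly be worse than their imputed values, taken as equal in both arms. Then, for the ETT minus EECP-ETT difference,

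true difference − imputed difference = (w_C − w_E) × d.

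All values of w and d below are assumptions.

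- w_C − w_E = 0.10: 0.10 × 2 = 0.2 to 0.10 × 6 = 0.6 points, or 7% to 22% of 2.71. The imputed analysis understates the EECP advantage.
- w_C − w_E = 0.05: 0.1 to 0.3 points, or 4% to 11%, in the same direction.
- w_C − w_E = −0.10: −0.2 to −0.6 points. The imputed analysis now overstates the EECP advantage.
- w_C = w_E: 0.

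**The case against.** **The ITT set stays primary and imputation keeps these patients in it.** This stands. A reader might infer that the rule defeats ITT, but the documents do not support that. Every randomised patient can still be analysed in the assigned arm. What changes is that some primary outcomes become imputed rather than observed.

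**The article never says the week-7 NIHSS is not collected after a condition (2) withdrawal.** This is also true. The loss is a strong inference from the words used, from the neighbouring conditions and from the contrast with the safety paragraph. The fix is needed partly because the text leaves it to inference.

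**The link to prognosis and to arm is conjecture.** In part. The article does not list the prohibited therapies, which the full protocol may do, and it does not name who decides on withdrawal under condition (2). A link to recovery is plausible but not shown.

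**The imputation model is unknown and may use more than baseline.** This stands as a limit. The article says only that multiple imputation is used; missing at random is the usual assumption, and details may be in the SAP. Symptomatic orthostatic hypotension, safety and session haemodynamics are recorded through the intervention weeks and could inform the model up to the exit. They are not NIHSS scores, however, and the outcome after the added therapy would remain unobserved.

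**A one-arm calculation gives a larger figure.** With 5% to 15% of the ETT arm withdrawn and scores 3 to 6 points worse, that arm's mean shifts by 0.05 × 3 = 0.15 to 0.15 × 6 = 0.90 points, or 6% to 33% of 2.71. This assumes no such exits in the other arm and no recovery through imputation, so it is a corner case and not an estimate.

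**Separate consent for each modality.** A reader might see a second route to loss in one arm in "Formal informed consent will be obtained prior to the initiation of each specific therapeutic modality", since only one arm is offered EECP. That sentence stands in the standard-care text for all participants, after a list of conventional therapies. Declining a modality is nowhere equated with withdrawing from the trial. Study design and Table 2 already place trial consent before the study period and before allocation. This forms no part of the point.

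**Conclusion.** The point holds in a limited form. As written, condition (2) takes randomised patients out of the trial for a post-randomisation event, while the safety paragraph keeps a comparable group under assessment. The likely result is a missing week-7 NIHSS for which there is no intermediate NIHSS to draw on. That weakens the primary ITT analysis and makes it depend on assumptions it could avoid.

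The size is unknown. Under the stated assumptions the bias is 0.2 to 0.6 NIHSS points for a 10-point difference in withdrawal, it can favour either arm, and it vanishes with equal shares and departures. Power on observed data falls from about 90% to between 88% and 83% only if these exits add 5 to 15 points to the budgeted loss. The text does not support a claim that the trial is biased towards EECP, or that any planned figure is wrong. The change is still worth making, because it concerns the primary endpoint and an outcome not collected cannot be supplied at analysis.

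**What to change.** Reconcile the Participants and Interventions sections on who remains in follow-up:

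- Remove condition (2) as a reason to leave the trial.
- Record the concomitant therapy or procedure, with its date, as a protocol deviation, and handle it in the per-protocol or a sensitivity analysis.
- Unless the patient withdraws consent to data collection, keep the week-7 assessment and analyse the patient as randomised.

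This concerns data collection only; it does not touch which treatments patients may receive or when the study intervention stops.

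The cost is a protocol amendment and the follow-up of probably a few more patients. The procedures exist already: bedside visits, telephone contact and flexible scheduling are described under Assessment schedule and retention strategies. Recruitment began in July 2024 and is ongoing (Trial status), so the change protects outcomes still to come. Those of patients already withdrawn may not be recoverable; their number, by arm and reason, should be reported.

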### Randomization and blinding

Enrolled participants will be randomly assigned in a 1:1 ratio to either the ETT training group (receiving conventional rehabilitation combined with ETT training) or the sequential EECP-ETT training group (receiving conventional rehabilitation combined with sequential EECP followed by ETT training). The randomization sequence will be computer-generated by an independent statistician using SPSS software, employing a variable block randomization design. Randomization will not be stratified according to any baseline characteristics. To ensure strict allocation concealment, sequentially numbered, opaque, sealed envelopes will be utilized. Due to the physical nature of the interventions, blinding of participants and administering therapists is unfeasible. However, to minimize detection bias, all outcome assessors and data analysts will remain strictly blinded to the group assignments throughout the trial.

